### Qualitative process studies

There will be two qualitative process studies. One will examine participants’ experiences of using the intervention and participating in the trial. Participants will be emailed the information sheet with an invitation to take part in this additional study. Eight to ten participants per cancer type (n=24–30) will be purposively sampled until saturation (by cancer type, age and gender). Participants will be invited to take part after they have taken part in the trial for at least 1–2 months. Additional consent will be sought for these studies. Interviews (face-to-face or by phone) will consist of open-ended questions to elicit detailed responses. Each interview will last approximately 60 min. These interviews will enable the research team to further assess the acceptability and helpfulness of the intervention and any barriers to engagement. Control participants will also be invited in the same way to participate in brief interviews to elicit qualitative feedback about the brief advice link they were given at baseline (the NHS LiveWell website) and the study.

The second qualitative process study will be conducted with Supporters, to explore their views of supporting patients in using Renewed online. This study will elicit perceptions of the initial training website, providing support to patients and the general study procedures. After at least 1–2 months of participation, support providers, GPs and any other primary care staff significantly involved in trial procedures or intervention delivery (n=20, or until saturation) will be invited to take part in this additional study. Focus groups, interviews or phone interviews will be held, depending on availability or else electronic (written) feedback will be requested.

In both process studies interviews will be recorded and fully transcribed. Transcriptions will be anonymised. To ensure that we remain open to, and grounded in, interviewee perspectives we will carry out inductive thematic analysis of all textual data,^58^ triangulated where appropriate with other trial data (eg, web usage), and with discussion among team members (including our PPI representatives) to elaborate our interpretations.^58^

### Handling of adverse events

It is very unlikely that there will be any adverse events during screening and questionnaire completion, given that screening online consists of answering questions; however, participants are repeatedly told that they can contact the research team who can signpost them to other support services as appropriate. Participants have the right to withdraw from the study at any time. If a participant withdraws having completed questionnaires, their data will be retained to evaluate potential differences and reasons for attrition, unless they ask us not to use their data. Should a participant be ineligible for the study for any reason, they are presented with a page of alternative support services.

Any serious adverse event (SAE) occurring to a research participant will be reported to the Ethics Committee where, in the opinion of the Chief Investigator, the event was related to administration of any of the research procedures, and was an unexpected occurrence. Non-serious AEs will not be collected. Pre-planned hospitalisation for example, for pre-existing conditions which have not worsened or elective procedures for a pre-existing condition will not be classed as an SAE. GP surgeries will inform the research team and/or the clinical trials unit of any SAEs within 24 hours of becoming aware of the event occurring. GP surgeries will be provided with a standard operating procedure and a form for SAE reporting. Reports of SAEs will be provided to the Committee within 15 days of the Chief Investigator becoming aware of the event. All SAEs will also be sent to the Trial Steering Committee.

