### Randomisation and blinding

After online screening, patients will complete online consent and baseline measures. LifeGuide software will then randomise each participant to one of the three study groups using computer-generated random numbers. Once randomised, participants will be informed of their allocation and, if in one of the intervention arms, given access to Renewed. Randomisation will be stratified by cancer type: breast/prostate/colon and by EORTC score (high/low QoL; 64 or less/65–85 taking 65 as the lower 25% CI from previous study data^36^). Blinding of randomisation is ensured by the use of automated computer software. Blinding of patients to the intervention is not possible. Participants will be informed online as to which group they have been allocated to immediately and will also be sent notification via email. Practice staff involved in the support arm of the trial will be notified by email when one of their patients is randomised to the Renewed + Support arm of the trial so that they can provide support.

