### Renewed accompanied by brief human support

Participants in the Renewed group with accompanying brief human support will receive support from a nurse or healthcare assistant (at their surgery where possible, or else a central support facilitator or research nurse employed by the study team where the practice are unable to provide their own support). ‘Supporters’ are able to view the Renewed intervention but do not need specific knowledge of Renewed content: Supporters will receive brief web-based training to learn how to provide support using the CARE approach (Congratulate, Ask, Reassure, Encourage^49 50^), which aims to help build patients’ autonomous motivation for engaging with the digital intervention and offline behavioural changes (eg, getting more active).

Three 10 minute support sessions will be offered in person, by phone or email. The first will be offered 2 weeks after initially logging on to Renewed. Supporters are also asked to send encouraging, supportive emails at weeks 2 and 4 after randomisation and templates are supplied for this. Follow-up support will be offered at 4 and 8 weeks after baseline. Not all participants will want support and they can choose whether or not to contact their Supporter; Supporters will keep a record of the frequency and nature of support they provide to participants. Participants can contact their Supporter through the website. Number and type (email/phone/face-to-face) of support contacts, as well as length of appointments, will be recorded.

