**Process measures**			
TAQ		x	
PEI			x
Website satisfaction and usage			x
PETS			x
Usage of other interventions during past year			x

Demographics include gender, age, marital status, years of education, ethnicity, height and weight and are taken at baseline;

EQ-5D-5L, Euro-Qol; EORTC QLQ-c30, European Organization for Research and Treatment of Cancer Quality of Life Questionnaire-c30 as primary outcome; FRRS, Fear of Relapse/Recurrence Scale; HADS, Hospital Anxiety and Depression Scale; MYCAW, Measure Yourself Concerns and Well-being; PA, Physical activity checker; PEI, Patient Enablement Instrument; Website satisfaction measure; PETS, Problematic Experiences of Therapy Scale; TAQ, Treatment Appraisal Questionnaire.

The primary outcome of QoL will be measured using the total score on the EORTC QLQ-c30.^35^ The EORTC has 30 items and contains five functioning subscales: physical, emotional, social, role and cognitive and eight symptom subscales: pain, fatigue, nausea and vomiting, dyspnea, sleep problems, loss of appetite, constipation and diarrhoea, financial impact and overall quality of life. Each item has a four-point response scale from ‘not at all’ to ‘very much’ and scores are calculated using a linear conversion to create a score from 0 to 100. It is one of the most widely used measures for health-related QoL in cancer research.^52^

The Fear of Relapse/Recurrence Scale^53^ has been modified to three items so that ‘I will probably have a relapse in the next 5 years’ and ‘I am certain that I have been cured of cancer’ are omitted as they do not apply to those on Active Surveillance. The Patient Enablement Instrument (PEI) was modified so that it asks about confidence and understanding relating to health as a result of using the website as opposed to receiving support from a doctor (PEI^54 55^). Data regarding website and/or app usage (eg, pages accessed, time spent on each page) will be downloaded using LifeGuide software. A medical record notes review will be conducted after 12 month follow-up to extract NHS and Personal Social Service use. This will enable collection of data pertaining to clinical status including cancer recurrence. Online questions will be used to collect patients’ personal costs. The EQ-5D-5L^56 57^ which measures medical QoL (QALY) will be collected at baseline, 6 months and 12 months. We will apply the UK tariff to translate the EQ-5D-5L to utility scores.

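### As described, SAE reporting runs through GP surgeries, but only the Renewed + Support arm has a described randomisation notice to the practice and extra staff contact, so SAE capture may be more complete in that arm

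*Protocol article*

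**What the plan says.** All references are to the protocol article.

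- **Handling of adverse events.** The reporting duty lies with the practices: "GP surgeries will inform the research team and/or the clinical trials unit of any SAEs within 24 hours of becoming aware of the event occurring". They are equipped for it: "GP surgeries will be provided with a standard operating procedure and a form for SAE reporting". Neither sentence is limited to an arm. Non-serious events are not collected. All SAEs go to the Trial Steering Committee, and those judged related and unexpected also go to the Ethics Committee.
- **Randomisation and blinding.** Screening, consent, baseline measures and randomisation take place online, and the result goes straight to the participant: "Participants will be informed online as to which group they have been allocated to immediately and will also be sent notification via email". For one arm there is also a message to the surgery: the supporting staff there "will be notified by email when one of their patients is randomised to the Renewed + Support arm of the trial", and the stated purpose is "so that they can provide support". No corresponding message is described for Renewed alone or usual care.
- **Renewed accompanied by brief human support.** This arm alone is offered three 10-minute sessions, and supporters are also asked to send emails at weeks 2 and 4. The supporter is a nurse or healthcare assistant at the surgery or, failing that, "a central support facilitator or research nurse employed by the study team where the practice are unable to provide their own support".
- **Measures.** "A medical record notes review will be conducted after 12 month follow-up to extract NHS and Personal Social Service use". The review is also to yield clinical status, including recurrence. No arm restriction is stated, and it is not described as a source of SAEs.

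**The concern.** A practice can report an SAE promptly only if it knows two things: that the event happened, and that the patient is in the trial. Practices know whom they invited. As the article describes the process, they are told who was randomised only in the support arm. That arm also has staff contacts at which an admission or a new diagnosis could come up. Both conditions for a report may therefore be met more often in one arm than in the other two.

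SAEs are the only adverse-event data the trial collects. If the Trial Steering Committee or a later report counts them by arm, human support could appear to carry more events than Renewed alone or usual care when the true rates are the same. Separately, if capture is low in the two arms without a notice, a real harm of Renewed alone would be harder to see.

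**Working it through.** The protocol article gives no SAE rate, no capture rate and no SAE comparison to reproduce. The check is a side-by-side reading of the sections, followed by an illustration under stated assumptions.

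**Step 1. What is described for each arm**

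| | Renewed + Support | Renewed alone | Usual care |
|---|---|---|---|
| Practice has SAE procedure and form | yes | yes | yes |
| Practice notified of randomisation | yes | not described | not described |
| Staff sessions and emails | offered | none | none |
| Notes review after 12 months | yes | yes | yes |

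Rows 2 and 3 differ by arm and bear on SAE reporting as described. Row 4 does not differ by arm, but the article does not link it to SAE reporting. Renewed alone and usual care match in every row.

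**Step 2. Effect on an observed ratio**

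Let *p* be the true SAE risk, equal in all arms, *c*S the share of SAEs reported in the support arm, and *c*O the share reported in each of the other two arms.

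- Observed ratio, support v usual care (or v Renewed alone) = (*p* × *c*S) / (*p* × *c*O) = *c*S / *c*O.
- Observed ratio, Renewed alone v usual care = *c*O / *c*O = 1.

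The true risk cancels, so the spurious ratio depends on the capture rates alone.

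**Step 3. Numbers**

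From the document: a total of 2500 (Sample size and power calculation). Assumed: three equal arms, so 2500 / 3 = 833.3 per arm; *p* of 10% or 5%; *c*S of 80%; *c*O of 80%, 60% or 40%.

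At 10% there are 833.3 × 0.10 = 83.3 true SAEs per arm. At 5% there are 833.3 × 0.05 = 41.7.

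| Capture, support v other | Expected reports at 10% | Expected reports at 5% | Spurious ratio |
|---|---|---|---|
| 80% v 80% | 66.7 v 66.7 | 33.3 v 33.3 | 1.00 |
| 80% v 60% | 66.7 v 50.0 | 33.3 v 25.0 | 0.80 / 0.60 = 1.33 |
| 80% v 40% | 66.7 v 33.3 | 33.3 v 16.7 | 0.80 / 0.40 = 2.00 |

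The first row matters as much as the others: if practices learn of all participants equally well and the extra contact brings nothing to light, there is no bias.

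**Step 4. Within the support arm**

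Where a central facilitator or research nurse gives the support, the practice gains no extra contact. The adverse-event section gives that supporter no stated duty to report. Capture may therefore also vary within the arm, and the gap to the other arms would be smaller where support is central.

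**The case against.** The strongest reply is that this argues from silence in a condensed article. The email to support-arm staff is there to start the support and does not claim to list everything practices are told. The SAE duty covers any research participant, and the procedure given to practices may well say how they identify participants in every arm. This stands to the extent that nobody can say practices *are* unaware of the other participants. It does not remove the point, because the extra staff contact is specific to one arm whatever else practices are told.

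A reader might infer three stronger things that the document does not support:

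- **That GP surgeries are the only possible source of SAE reports, and that practices are never told of participants in the other arms.** The article states neither. These are the only route and the only notice it describes.
- **That any between-arm safety comparison is biased.** Renewed alone and usual care are in the same described position, so their contrast is not distorted by this mechanism. Low capture in both would cost sensitivity, which is a different problem.
- **That the Trial Steering Committee will see an excess in the support arm.** No by-arm SAE analysis is stated, and the article does not say that the Committee receives SAEs by arm.

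It is also fair to say that the asymmetry may be modest. Support is optional, brief, possibly by email, and scheduled in roughly the first 8 weeks. Deaths and admissions can reach a practice by other means. The notes review is already a source that does not depend on arm, although it comes too late for 24-hour reporting.

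**Conclusion.** The point holds in a limited form. As described, SAE ascertainment may be more complete in Renewed + Support than in the other two arms, so an SAE tally that sets that arm against either of them could mislead. The size cannot be determined from the document. The spurious ratio is 1.0 under equal capture and 1.33 or 2.0 under the assumed capture rates of 80% v 60% or 40%; none of these rates has a source in the plan. The illustration also assumes equal true risk in all arms; the event counts, but not the ratios, assume equal arm sizes. The primary quality-of-life analysis is not touched. The matter is worth acting on because SAEs are the only adverse-event data collected and the means of an arm-neutral summary are already planned.

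**What to change.** 1. Base any SAE summary by arm on the notes review after 12 months. Add deaths, unplanned admissions and new cancer events to the extraction form. Present GP-reported SAEs separately, labelled as expedited reports.
2. Send practices the same enrolment notice for participants in all three arms, so that the 24-hour duty can operate equally. The email that starts the support can stay as it is.
3. Extend the reporting duty to central support facilitators, and to research staff who learn of an event.

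The cost is a few extra fields on a review that is already planned, one more automated message, and a change to the SAE procedure. The downside is that practices learn of participation in every arm.

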### Dissemination

The results of this trial will be published in peer-reviewed journals and through conference presentations. Press releases will be utilised to disseminate the findings to the general public and the findings will also be sent to the GP surgeries who participate and to those participants who request them. Social media networks connected to the research group (eg, Twitter) will be used to disseminate published research. If proven effective, Renewed will be developed with service providers and charities to explore mechanisms through which it can be made available to patients.
